## Abstract

**Background:**

Persistently elevated blood pressure (BP) is a leading risk factor for cardiovascular disease development, making effective hypertension management an issue of considerable public health importance. Hypertension is particularly prominent among African Americans, who have higher disease prevalence and consistently lower BP control than Whites and Hispanics. Emergency departments (ED) have limited resources for chronic disease management, especially for under-served patients dependent upon the ED for primary care, and are not equipped to conduct follow-up. Kiosk-based patient education has been found to be effective in primary care settings, but little research has been done on the effectiveness of interactive patient education modules as ED enhanced discharge for an under-served urban minority population.

**Methods/Design:**

Achieving Blood Pressure Control Through Enhanced Discharge (AchieveBP) is a behavioral RCT patient education intervention for patients with a history of hypertension who have uncontrolled BP at ED discharge. The project will recruit up to 200 eligible participants at the ED, primarily African-American, who will be asked to return to a nearby clinical research center for seven, thirty and ninety day visits, with a 180 day follow-up. Consenting participants will be randomized to either an attention-control or kiosk-based interactive patient education intervention. To control for potential medication effects, all participants will be prescribed similar, evidenced-based anti-hypertensive regimens and have their prescription filled onsite at the ED and during visits to the clinic. The primary target endpoint will be success in achieving BP control assessed at 180 days follow-up post-ED discharge. The secondary aim will be to assess the relationship between patient activation and self-care management.

**Discussion:**

The AchieveBP trial will determine whether using interactive patient education delivered through health information technology as ED enhanced discharge with subsequent education sessions at a clinic is an effective strategy for achieving short-term patient management of BP. The project is innovative in that it uses the ED as an initial point of service for kiosk-based health education designed to increase BP self-management. It is anticipated findings from this translational research could also be used as a resource for patient education and follow-up with hypertensive patients in primary care settings.

**Trial registration:**

ClinicalTrials.gov Registration Number: NCT02069015. Registered February 19, 2014.

## Background

As a leading risk factor for cardiovascular disease, high blood pressure (BP) costs an estimated $47.5 billion annually in health-care expenditure [1]. Prevalence of hypertension among U.S. adults in 2003–2010 was 30.4 % (66.9 million) and an estimated 53.5 % (35.8 million) of these did not have their blood pressure under control. About 90 % of those with uncontrolled hypertension had a usual source of health care, insurance, and had visited a physician in the past year, suggesting missed opportunities for improving BP control [2]. Additionally, African-American adults, the clinic population for this study, have the highest prevalence of hypertension (44 %) in the United States as well as higher disease prevalence and consistently lower blood pressure control than Whites and Hispanics [3].

While physicians prescribe antihypertensive medications, a critical component of effective BP control rests with the individual. In one study, awareness, knowledge, and attitudes were more important than medication costs in achieving BP control [4]. Other individual factors such as chronic stress may be related to hypertension prevalence and BP control, especially for African-Americans [5]. Along with individual factors, environmental factors play a major role in BP control. For example, neighborhood disadvantage, measured by an index that includes the number of households living below the poverty line, has been highlighted as a factor that is significantly associated with poor blood pressure control in African-American older adults [6].

Because of the increasing prevalence of hypertension across ages, particularly among African-Americans, strategies to address blood pressure control are a critical public health issue [7, 8]. Population-based initiatives for hypertension prevention and control that leverage multiple community resources and address individual and socioeconomic factors are well positioned to have far reaching impacts on public health and are a high priority [9, 10]. Within the context of public health and the epidemiological paradigm of patient (host), emergency department (agent) and health service delivery (environment), the Haddon matrix has been further adapted to address the core elements of utilizing an urban emergency department as a portal for research and practice of population-based hypertension screening, intervention and delivery [8] (Table 1).

**Table 1 Tab1:** Population-based systems approach to hypertension control

	Patient (Host)	Emergency department (Agent)	Health service delivery (Environment)
Precedent	Health belief/behavior	Treatment protocols	Public transportation
	Socioeconomic status	Physician knowledge	Economic climate
	Health Literacy	Case management	Educational opportunities
	Perceived disease severity		
Intervention	Treatment preferences	Patient management	Proximity to primary care
	Health status	Practice patterns	Quality of health services
	Healthcare coverage	Competing priorities	Contextual empathy
	Perceived level of risk	Patient discharge	Patient education
Antecedent	Self-efficacy	Referral to chronic care	Health education
	Clinical outcome	Provision of follow-up	Health information technology
			Access to medical care

Adaptation of the Haddan Matrix from Levy and Cline, 2009 [11]

Highly activated patients take more responsibility and acquire disease-specific knowledge and skills, thus promoting self-management and facilitating effective interactions with the health care system while also encouraging engagement in healthy behaviors [11–13]. Studies suggest that increased patient activation is strongly associated with a variety of self-management behaviors; however, there is little understanding of what interventions will improve activation [14]. Motivation and a sense of priority for patients to perform challenging self-care activities and implement discharge instructions may also play significant roles [15].

These factors are addressed in the Information-Motivation-Behavior (IMB) model, an evidence-based comprehensive health behavior change framework that has been applied to understanding engagement in a variety of health behaviors [16–19]. Patient education information includes knowledge about risk factors and behavior to modify risk. Motivation encompasses personal attitudes and beliefs, social norms and support systems. Behavioral skills include learning the specific skills needed to facilitate lifestyle modification. Self-efficacy provides the foundation for enacting these skills; patients are more likely to succeed if they self-monitor/evaluate their lifestyle progress, such as in weighing themselves regularly [20]. Barriers play an important role, influencing all three elements, but particularly personal motivation [17, 18, 21]. To be successful, interventions should focus on *modifiable* behaviors which should result in positive behavioral change [22].

Within the context of this modified IMB model, patient education delivered via information technology, i.e., interactive kiosks, can be a useful tool to promote hypertension control. Touch screen kiosks have been used with success as a provider-driven approach to deliver health education, improve knowledge, promote self-assessment, and monitor BP [23–30]. Importantly, those at greatest risk for poor BP control (i.e., underserved and minority populations) have reported satisfaction with interactive kiosk use [26, 27, 31], making it a viable option for studies targeting hypertension control in such groups.

With the IMB model as our conceptual framework (Fig. 1), the proposed study will examine the application of patient education/health education delivered through health information technology to improving BP control and self-monitoring behavior. In the form of a touch screen interactive kiosk, participants in our study will receive a self-paced series of brief informational sessions about hypertension and guided through the process of taking their own BP using the attached blood pressure monitor. These multiple brief sessions are expected to increase motivation and behavioral skills. Using the kiosk to self-monitor and track their progress repeatedly is also expected to increase self-efficacy for using behavioral skills leading to increased patient activation and medication adherence for the health outcome of blood pressure control.

**Fig. 1 Fig1:**

Kiosk-based patient education as enhanced discharge: IMB conceptual model

Results from a prior investigation by our research team in a clinic population of underserved, largely African-American adults indicated that brief health education sessions delivered by a touch screen kiosk with an attached BP monitor resulted in an overall change in BP that was statistically significant. In this feasibility study, at three month follow-up, 8 of the 25 participants (32 %) with uncontrolled BP at baseline had their BP under control (i.e., at or below 130/80) [20, 32]. These results paralleled other health studies, including one focused on diabetes education, in which participants reported that the health information technology delivered was equal or better than that received from healthcare providers because the information contained both audio and text, was step-by-step and logical, under their control, and they were able to learn something new in a limited time [33, 34].

Approximately 25 % of ED patients nationally have hypertension and 46 % of them are unaware of being hypertensive [35, 36]. The present study focuses on ED patients with uncontrolled hypertension the point of discharge. A previous study done by our team with African-American patients within this population indicated that subclinical hypertensive heart disease was highly prevalent (90.6 %), suggesting the need for focused efforts to reduce pressure-mediated consequences of hypertension [7]. Thus, the ED is an appropriate entry point to identify high-risk patients for whom our proposed intervention would be most beneficial.

## Methods

### Study design and aims

Achieving Blood Pressure Control Through Enhanced Discharge (AchieveBP) is a behavioral patient education intervention. It is a longitudinal, randomized controlled study in which ED patients with uncontrolled hypertension receive either an educationally enhanced or a standard discharge procedure. Study outcomes are assessed at baseline, 30, 90, and 180 days post ED discharge.

The design and conduct of the study adheres to the Consolidated Standards of Reporting (CONSORT) guidelines [37]. The study was approved by the Wayne State University Medical Institutional Review Board (M1, IRB#050213M1F) on 23 July 2013, and is registered with ClinicalTrials.gov (#NCT02069015). The study is administered through the Department of Family Medicine & Public Health Sciences in partnership with the Department of Emergency Medicine at the Wayne State University School of Medicine. Results of this study will be disseminated via scientific forums, including peer-reviewed publication and presentations at national and international conferences.

The primary aim of the study is to determine if integrating kiosk-based patient education via health information technology into the ED discharge process, coupled with additional educational sessions outside the ED will improve BP control compared to the usual discharge process. The secondary aim is to explore the relationship between patient activation, self-management behaviors (e.g., BP medication adherence), and health care utilization (i.e., return hospital emergency department visits). Cost effectiveness of the intervention will be assessed as well.

### Study population

Adults (age > 18 years) capable of utilizing the kiosk who have self-reported histories of hypertension and present with uncontrolled BP to the ED (>140/90 for non-diabetics and >130/80 for diabetics) will be targeted for recruitment. ED staff, familiar with the study eligibility criteria, will provide initial screening to identify potential study participants. As primary exclusion criteria, those patients with a diagnosis of end-stage renal disease, cognitive impairment, or requiring hospitalization after ED discharge will not be eligible for study participation.

### Consent and Randomization

Figure 2 shows the flow of the participants through the study. Pre-screening will be conducted by trained research assistants. Prior to consent, patients will be informed the enrollment process could take about an hour to complete. Once identified, research staff will meet with the potential participants to describe the study, answer questions, and obtain consent. After signed consent, project staff will use the CAGE questionnaire to screen for substance abuse disorders. Those who score two or more will be considered ineligible and dropped from the study. Up to 200 adults will be enrolled (i.e., 100 per study arm with oversampling by 50 % to account for attrition). A second BP reading will be obtained prior to randomization to verify that the high BP readings taken during initial screening remain at the eligibility level.

**Fig. 2 Fig2:**
[figure not shown]
Study flow chart

Given the differential definition for blood pressure control, a stratified random sampling procedure will be used, based on self-reported diabetic diagnosis. A block randomization schedule will be developed using a separate computer-generated random number table for diabetic and non-diabetics. Once diabetic status is determined, research staff will use the appropriate table to assign the participant to one of two study arms:

• Standard discharge (Attention control group) who will receive the ED’s usual discharge instructions for follow-up care. These materials typically include an accounting of major procedures and tests performed during the emergency department visit, principal diagnosis at discharge/chief complaint, patient instruction, follow-up care and medication/prescription.

• Intervention group, who, in addition to receiving the standard printed materials, will also receive a hypertension curriculum delivered via a touch screen kiosk with attached blood pressure monitor.

### Study procedures

Once randomized, participants will complete their baseline assessments at the ED. Participants randomized into the intervention arm will be shown how to use the kiosk to answer questions and will complete the first health education module before leaving the ED.

To control for medication effects on blood pressure readings, all participants, regardless of study arm, will be prescribed a similar, evidence-based antihypertensive regimen [38], according to the algorithm illustrated in Fig. 3. Additionally all participants will receive an initial seven day medication supply at the conclusion of their ED visit. Participants on existing antihypertensive medication will have their medication adjusted to be in keeping with the study protocol. BP medication titration and side effect monitoring will occur at 7, 30, and 90 day post enrollment. All participants will receive primary care referrals as appropriate.

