**Fig. 3 Fig3:**
[figure not shown]
Anti- hypertensive regimen. Note: Medications are prescribed in the absence of any contraindications

The study will be conducted by a multi-disciplinary team of trained emergency clinical medicine and public health researchers in two urban health environments: an emergency department and an academic clinical research center. Under the supervision of a research physician, patient screening, enrollment, baseline assessment and the first education intervention will be conducted by research assistants at the emergency department. The research physician will then review medication orders and provides instructions for the participant at enrollment. All subsequent study visits will occur at the clinical research center (CRC) about one mile away. At the beginning of each visit, the research physician and his clinical research team will review medication side effects, conduct pill counts and provide medication refills at seven, thirty and ninety day visits, with a three month prescription at the 180 day follow-up. Graduate level public health students will conduct post and follow-up interviews and facilitate patient education for the intervention group.

To promote retention, reminder calls and/or email will be done several days in advance and contact information will be updated at each visit. Both groups will be encouraged to monitor their blood pressure on their own and follow-up with a primary care physician. Participants missing visits and not responding to up to three reminder communication will be considered lost to follow-up. Participants will be withdrawn from the study for reasons such as withdrawing consent or moving too far away.

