#### Secondary outcome measures

Secondary outcome measures include patient activation, medication adherence, health-related quality of life, and cost effectiveness. In regard to cost-effectiveness, to understand the financial burden associated with study participation, we will conduct a brief survey with participants at the completion of the study about costs they have incurred. These data will be combined with additional measures (e.g., ED and hospital recidivism) compiled by review of hospital records to derive estimates of the cost effectiveness of a kiosk-based approach to ED discharge, from a public health perspective.

Patient activation will be measured by The Patient Activation Measure (PAM) [40], a unidimensional thirteen item scale assessing patient knowledge, skill and confidence in self-management behaviors. Patients rate how strongly they agree/disagree with each item. Besides obtaining an activation score, responses can be used to stage individuals along an activation continuum: (1) believes active role is important, (2) confidence and knowledge to take action, (3) taking action, and (4) staying the course under stress. All participants will use the kiosk to complete the tool at baseline, 90, and 180 days post enrollment.

Medication adherence using the Morisky Medication Adherence Scale (MMAS) will be used to assess self-management behavior. The eight item MMAS, a self-report assessment tool shown to have a statistical association with antihypertensive medication refill rates, will be completed at 30, 90 and 180 days [41], also through the kiosk. Clinical research staff will conduct pill counts as part of medication monitoring at each follow-up appointment. Using fixed denominators based on a known quantity of medication dispensed at the prior evaluation, drug-specific and overall measures of antihypertensive therapeutic intensity will be derived.

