
In addition to assessing the primary outcome, the project will assess two secondary hypotheses related to patient activation. Analysis of covariance using the baseline activation score as covariate will be conducted to test for significant differences in patient activation scores between groups at the 180 day assessment. Pearson correlations and subsequent multiple regression analyses will test the association between patient activation scores and engaging in self-monitoring of blood pressure, medication adherence scores, demographics, and number of subsequent emergency department and primary care visits. Logistic regressions will explore differences in participant study completion and in obtaining BP control.

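### Baseline assessments follow randomisation, so the self-reported activation score used as the day-180 ANCOVA covariate, and possibly the baseline blood pressure, can be influenced by allocation

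*Protocol article*

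**What the plan says.** All references are to the protocol article.

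- **Order of steps.** Study procedures: "Once randomized, participants will complete their baseline assessments at the ED". The next sentence has the intervention arm shown how to use the kiosk and completing the first module before leaving the ED.
- **Who does it.** Later in Study procedures: "patient screening, enrollment, baseline assessment and the first education intervention will be conducted by research assistants at the emergency department".
- **What precedes randomisation.** Consent and Randomization puts consent, the CAGE screen and a repeat BP, checked against the entry limits, first: "A second BP reading will be obtained prior to randomization to verify that the high BP readings taken during initial screening remain at the eligibility" (quote cut short).
- **How the arm is assigned.** Same section: "Once diabetic status is determined, research staff will use the appropriate table to assign the participant to one of two study arms".
- **Baseline PAM.** Secondary outcome measures: "All participants will use the kiosk to complete the tool at baseline, 90, and 180 days post enrollment".
- **Its use.** Statistical analysis: "Analysis of covariance using the baseline activation score as covariate will be conducted", for the comparison of activation at 180 days.
- **Blood pressure.** Study design and aims counts baseline as an outcome time, with 30, 90 and 180 days. The primary outcome section has the BpTRU device used at every assessment. Statistical analysis makes the linear group x time interaction the main effect for continuous BP and also speaks of changes in readings. The article does not say whether the baseline value is the qualifying reading or one taken after randomisation.

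**The concern.** A baseline covariate earns its place in ANCOVA because randomisation makes it independent of treatment. That holds only if it is measured before allocation, or cannot respond to allocation. PAM meets neither condition here. It asks how strongly patients agree with statements about their own knowledge, skill and confidence, and it is answered after the arm has been assigned. A participant who knows that education is coming may rate these higher, or may rate them lower on seeing how much there is to learn. A participant assigned to usual discharge may also shift. Staff who know the arm may handle the session differently.

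If the arms differ at baseline because of allocation, ANCOVA treats that difference as chance imbalance and adjusts part of it away. The day-180 activation contrast is then biased, and the data cannot separate this from ordinary imbalance. Any BP analysis that uses a post-randomisation reading as its starting point has the same weakness. The order of steps is stated in the article, so this is not a detail left to a fuller document.

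**Working it through.** **1. The plan's own figure.** Inputs from Statistical analysis: difference 6 mmHg, SD 12 mmHg, one-sided alpha 0.05, 50 per group.

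Power = Phi(6 / (12 x sqrt(2/50)) - 1.645) = Phi(2.5 - 1.645) = 0.804. A noncentral t calculation gives 0.799. The stated 0.80 is reproduced. Moving baseline earlier changes no sample-size figure.

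**2. PAM covariate.** Let allocation shift baseline PAM by x in the intervention arm, and let b be the within-arm slope of the day-180 score on baseline. The adjusted contrast is (difference at day 180) - b x (difference at baseline), so the shift adds -b*x. A rise in the intervention arm's baseline hides benefit; a fall, or a rise in the control arm, creates apparent benefit.

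The documents give neither x nor b. Assumed ranges: x = 0.1 to 0.3 SD and b = 0.3 to 0.7, with equal SDs at the two times so that b equals the correlation. The last column is the one-sided type I error when the bias favours the intervention: 1 - Phi(1.645 - bx x sqrt(50/2) / sqrt(1 - b^2)). It borrows the 50 per group and one-sided 0.05 from the BP calculation, because the article gives none for PAM.

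| b | x (SD) | size of bias (SD) | type I error |
|---|---|---|---|
| 0.3 | 0.1 | 0.03 | 0.07 |
| 0.3 | 0.3 | 0.09 | 0.12 |
| 0.5 | 0.1 | 0.05 | 0.09 |
| 0.5 | 0.3 | 0.15 | 0.22 |
| 0.7 | 0.1 | 0.07 | 0.12 |
| 0.7 | 0.3 | 0.21 | 0.43 |

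In the other direction the same bias costs power. These figures show sensitivity; they do not estimate what will happen.

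**3. Blood pressure, only if the analysis baseline is a post-randomisation reading.** Assessment days are 0, 30, 90 and 180, with mean 75. The deviations are -75, -45, 15 and 105, and their squares sum to 5625 + 2025 + 225 + 11025 = 18900. In an ordinary least-squares slope with complete data, the day-0 reading has weight -75/18900 per day, or -75/18900 x 180 = -0.71 over 180 days. An assumed 3 mmHg arm-specific shift at baseline alone therefore moves the 180-day slope contrast by 0.71 x 3 = 2.1 mmHg, against the planned 6. A simple change score would carry the full 3 mmHg. Missing visits or another covariance structure would change the weight.

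**4. The dichotomous endpoint.** BP control at 180 days compares the day-180 reading with fixed limits (140/90, or 130/80 for diabetics). No baseline value enters, so the bias in an unadjusted comparison of these proportions is zero.

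**The case against.** Several points on the other side are sound.

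- The headline endpoint, BP control at 180 days, uses no baseline value. This stands, and it limits the reach of the concern.
- The qualifying BP is taken before randomisation, and BpTRU readings are automated and started by the patient. Assessor influence on BP is therefore small, and a clean baseline may already exist. This stands, but the article does not say which reading the model uses.
- Baseline assessments are mentioned before kiosk training and module 1, and both arms complete PAM on the kiosk. Exposure to the module before PAM is therefore not shown, and use of the kiosk for PAM is not in itself a difference between arms. This also stands. Knowledge of the arm is enough for the concern, however, and the stated order permits it.
- The sizes of the shift and the slope are assumed. That is so, which is why they are given as ranges.

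A reader might go further and infer that staff read assignments from an open table, can foresee the next one in a blocked list, and can steer who enters each arm. The article does not support this. It says only that staff use the table for the relevant stratum. It does not say that upcoming assignments are visible, and a condensed article may leave concealment to the full protocol. Nor can the timing of baseline alter who is in each arm; that would be a separate question.

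**Conclusion.** The concern holds in a limited form. The article fixes an order in which a self-reported score is collected after allocation and is then used as if it were a pre-treatment covariate. The firmest consequence is for the day-180 activation comparison, a secondary hypothesis: a bias of -b*x, or 0.03 to 0.21 SD in either direction under the assumed ranges. The continuous BP analysis is exposed only if its baseline is a post-randomisation reading; an assumed 3 mmHg shift would then move the slope contrast by about 2.1 mmHg, under ordinary least squares with complete data. The unadjusted 180-day control proportion is unaffected, and nothing in the article shows that the make-up of the arms is compromised. This does not undermine the trial's main result, but it is worth correcting before enrolment, because analysis cannot recover an uncontaminated baseline afterwards.

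**What to change.** Within the same ED visit, use this order: consent; CAGE; qualifying BP; baseline BpTRU reading, PAM and baseline interview; randomisation; then kiosk training and module 1 for the intervention arm. Release the assignment only after eligibility and all baseline measures are recorded. State in the analysis section that baseline BP is the BpTRU reading taken before randomisation and that baseline PAM is the score completed before randomisation.

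The change adds no measurements, staff or visits and leaves the planned numbers as they are (50 per group analysed, 100 per arm enrolled). The cost is baseline time spent on a few patients who are then not randomised. That number should be small, because the CAGE screen and the qualifying BP would already have removed ineligible patients. If some patients have already been enrolled under the stated order, record for each whether PAM and BP preceded allocation. For those whose PAM followed it, report the day-180 activation comparison without baseline adjustment beside the planned ANCOVA.
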